#### Blinding

The field team are aware of which practices are in which arm, because they must mail or invite participants to the relevant intervention. However, patient and practice details are pseudonymised. All cleaning and processing of data are carried out on the whole database (*i.e*., all three arms) simultaneously. We will do this by only revealing the arm allocation variable at the end of the study. We try to minimise access to signature data that would allow the arms of the study to be differentiated. (*e.g*., if an analyst knew the precise list size of one practice in the study.) However, we only plan to reveal this variable when it is needed for final comparison between arms.

### Statistical analysis

Processed data extracted from GP practices and survey data using questionnaires will be imported onto the SPSS or a compatible software system. The data analysis will be conducted in three stages:

### Univariate and bi-variate analyses

1. We will document the recorded prevalence of CKD, as defined by socio-demographic (*e.g*., age, gender, ethnicity, deprivation scores).

2. We will document the level of confidence of primary care practitioners in the management of CKD stage three to five as defined by age, role, and the characteristics of the GP practices.

3. We will compare the recorded management of CKD Stage 3 – 5 in the participating GP practices with national and local guidelines.

4. We will document the recorded key co-morbidities of CKD stage three to five (*e.g*., diabetes, ischaemic heart disease etc).

5. We will compare the recorded management of key co-morbidities in the participating GP practices with national and local guidelines.

6. We will document the association between management of CKD using BP medication and falls.

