### Clinical and laboratory markers

1. Case definition using eGFR: We will define cases using the internationally accepted definition used by NKF Kidney Disease Outcomes Quality Initiative (KDOQI) [23], the same definition is used by NICE [4]. We will identify cases recorded since the standardisation of creatinine recording in 2006. However, we will also undertake a sensitivity analysis, including how prevalence changes when the date or number of readings are changed.

2. BP: We will measure the proportion of people in each arm with hypertension and CKD who achieve at least a ≥ 5 mmHg reduction in systolic BP. The reduction of mean systolic BP (the primary outcome measures) could be distorted in a number of ways.

3. Recording and management of key co-morbidities: diabetes and its complications; ischaemic heart disease; heart failure; obstruction/lower urinary tract symptoms.

4. Recording and management of other cardiovascular risk factors: smoking status; lipid management; proteinuria; anaemia; glycated haemoglobin and microalbuminuria in people with diabetes.

5. Serial measures of serum creatinine concentration and eGFR: to explore natural history and look for cases of accelerated decline (defined as a reduction of eGFR of >5 ml/min/1.73 m^2 ^in one year; or >10 ml/min/1. 73 m^2 ^in five years) [4].

6. Recording of death and cause of death: Although this is incompletely recorded, we will attempt to capture any recording as we expect mortality among hypertensive people over the period of the study. There may be a higher mortality among those who are in the control than intervention arms.

7. Avoiding harm: We wish to monitor whether BP reduction is associated with an increased number of falls particularly in older people. Most people with CKD are elderly and at potential risk for falls. Notwithstanding the results of recent systematic reviews that failed to show an association between falls and anti-hypertensive medication [25,26], this remains a genuine concern to some practitioners, and one that we propose to examine. A falls dataset will be devised and integrated into the renal dataset. We will investigate the relationship with use of ACE inhibitors and angiotensin II receptor blockers and systolic BP below 120 in CKD.

8. Medicines management

8. a. Use of drugs/therapy that affect renal function (for example non-steroidal anti-inflammatory drugs)

8. b. Use of ACEI and angiotensin II receptor blockers to control hypertension

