### Stopping rules

Although negative effects are unlikely, any suspected negative effects will be investigated and the study suspended, pending review. The principal safety monitoring activities will be: the observation for falls in people newly started on additional BP lowering drugs; and to identify whether there is any relationship between systolic BP and rate of falls.

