### Longitudinal data analyses

The temporal dimension of the recorded clinical data collected contemporarily offers an opportunity for analyses of the natural history and the disease course of CKD. The data have an advantage of being free from bias from retrospective recall, and allow the follow-up of the full spectrum of the impact of contributory risk factors on and outcomes for people with CKD. A particular interest is the association between management of CKD, the rate of change of eGFR, falls, and the outcomes of CKD.

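### Every stated falls analysis relates falls to a post-randomisation exposure; no comparison of falls by randomised arm is stated, for the final analysis or for safety monitoring

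*Protocol article*

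**What the plan says.** The protocol article describes an analysis of falls in four places.

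- Clinical and laboratory markers, item 7 (a secondary outcome under avoiding harm): "We wish to monitor whether BP reduction is associated with an increased number of falls particularly in older people", followed by "We will investigate the relationship with use of ACE inhibitors and angiotensin II receptor blockers and systolic BP below 120 in CKD".
- Stopping rules, where two principal safety monitoring activities are named. One concerns BP level: "to identify whether there is any relationship between systolic BP and rate of falls". The other concerns new drug treatment: "the observation for falls in people newly started on additional BP lowering drugs". The same section provides that "any suspected negative effects will be investigated and the study suspended, pending review".
- Univariate and bi-variate analyses, item 6: "We will document the association between management of CKD using BP medication and falls".
- Longitudinal data analyses: "A particular interest is the association between management of CKD, the rate of change of eGFR, falls, and the outcomes of CKD".

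Multivariate techniques states two comparisons between arms, for mean systolic BP and for practitioner confidence. Falls are in neither. Appendix 2, item 7, will look for more falls and for other harmful consequences of the intervention, but names no comparator. Appendix 3 lists a falls dataset covering falls, likely fragility fractures and new osteoporosis among the extracted data.

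**The concern.** The trial's own harm question is whether guidelines with prompts, or audit-based education, lead to more falls than usual practice. BP drug use, achieved BP and systolic BP below 120 are all reached after randomisation, by a clinician's decision or through the patient's state of health. Age, frailty and conditions such as heart failure plausibly affect both these exposures and falls. Item 7 itself observes that CKD patients are mostly elderly and at potential risk of falling. The bias can run either way: ill patients with low pressure may make treatment look harmful, and withholding drugs from frail patients may make it look safe. The Appendix 3 overview lists no direct measure of frailty, and the falls analysis in the statistical section sits in the univariate and bivariate stage.

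A rate of falls among people newly started on drugs also misses part of the question. An intervention could leave that rate unchanged and still cause more falls by increasing the number of people started.

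The monitoring has the same weakness. A suspected negative effect can suspend the study, yet neither monitoring activity has a randomised reference group. A confounded signal could stop the trial, or a real excess in an active arm could go unseen.

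**Working it through.** **1. Each falls analysis and its exposure**

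| Section | Falls related to | Fixed by randomisation? | Arm comparison stated? |
|---|---|---|---|
| Clinical and laboratory markers, item 7 | BP reduction; ACE inhibitor/ARB use; systolic BP below 120 | No | No |
| Stopping rules | New BP drugs; systolic BP level | No | No |
| Univariate and bi-variate analyses, item 6 | BP medication | No | No |
| Longitudinal data analyses | Management of CKD | No | No |
| Appendix 2, item 7 | No comparator named | – | No |

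The method is therefore stated four times, each time as an association.

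**2. The plan's own figure.** The only sample size for the trial comparison is for systolic BP (Sample size section): SD of practice means 3.77 mmHg, difference 3 mmHg, 5% level (taken as two-sided), 80% power.

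n per arm = 2 × (1.96 + 0.84)² × 3.77² / 3² = 2 × 7.84 × 14.21 / 9 ≈ 24.8, so 25 practices. The stated 25 reproduces (power 80.3% by the normal approximation, 78.7% with the t distribution). No event rate, ICC or power is given for falls.

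**3. What a falls comparison by arm could detect.**

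Inputs from the article: 25 practices per arm in the core trial (35 with the questionnaire practices), about 500 CKD patients per practice, ICC about 0.03 for systolic BP. Assumptions: two-year recorded falls risk of 2%, 5% or 10% under usual practice; falls ICC 0.01 to 0.05; one pairwise comparison at two-sided 5% with 80% power.

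- Design effect = 1 + (500 − 1) × ICC. At 0.03: 1 + 499 × 0.03 = 15.97.
- Effective patients per arm = 25 × 500 / 15.97 = 12,500 / 15.97 ≈ 783.
- The smallest detectable p1 satisfies (p1 − p0) / √{[p0(1 − p0) + p1(1 − p1)] / n_eff} ≈ 2.80.
- With p0 = 0.05 and n_eff = 783, p1 = 0.0856. The standard error is √[(0.0475 + 0.0783) / 783] ≈ 0.0127, and 0.0356 / 0.0127 ≈ 2.8. The risk ratio is 0.0856 / 0.05 ≈ 1.71.

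| Practices per arm | ICC | Design effect | Effective n per arm | RR at 2% risk | RR at 5% risk | RR at 10% risk |
|---|---|---|---|---|---|---|
| 25 | 0.01 | 5.99 | 2,087 | 1.70 | 1.41 | 1.28 |
| 25 | 0.03 | 15.97 | 783 | 2.26 | 1.71 | 1.47 |
| 25 | 0.05 | 25.95 | 482 | 2.70 | 1.94 | 1.61 |
| 35 | 0.03 | 15.97 | 1,096 | 2.02 | 1.59 | 1.39 |

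Restricting to a subgroup changes this little if the risk is the same, because the number of practices is what limits precision. With 250 patients per practice, ICC 0.03, 25 practices and 5% risk, the detectable ratio is 1.74.

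**4. Can arms be compared during the study?** The Blinding section says "We will do this by only revealing the arm allocation variable at the end of the study". Allocation concealment explains that the analysis table already separates practices into three arm groups without naming the arms. A table of falls by masked arm is thus possible at any extraction.

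**The case against.** The strongest reply is that the stated comparisons are not a complete list. Clinical and laboratory markers, item 2, measures the proportion in each arm with a systolic fall of at least 5 mmHg, and that analysis does not reappear in the statistical section. Falls are a secondary outcome of a trial to be analysed by intention to treat and reported under the cluster extension of CONSORT (Data quality assurance). A fuller protocol or analysis plan may tabulate every secondary outcome by arm. This stands as far as it goes: a reader might infer that the arm comparison has been ruled out, and the article does not support that. It is not stated. The point survives because the method for falls is stated, four times, and is never the randomised one.

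A reader might also infer that blinding leaves the monitoring without a comparator. It does not. Labels are withheld, but the masked arm groups are available, and labels are released for the final comparison.

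Thirdly, the associations answer a question the protocol poses, namely practitioners' worry about antihypertensive drugs and falls, and item 6 claims only to document an association. That is fair, and the associations can stay. They do not show whether the interventions cause falls.

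Finally, the arm comparison is not free of bias. Randomisation removes confounding of allocation, but falls come from routinely coded records, and the year-two themes include falls, which could prompt recording in the active arms. Nor is it sensitive: nothing in the article suggests that a BP difference near 3 mmHg would raise falls by 40 to 70%. Both limits should be stated with the result.

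**Conclusion.** The point holds in this form: for the main named harm, the protocol article states only analyses against post-randomisation exposures and states no comparison by randomised arm, at the end of the trial or for the monitoring that can suspend it. Followed as written, it would give a confounded answer to whether the interventions cause falls.

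The choice of analysis is established from the text alone. The power figures rest on assumed falls risks and ICCs, normal approximations and equal practices of 500 patients. On those terms, with 25 practices per arm and a 5% risk, the detectable risk ratio runs from 1.41 (ICC 0.01) to 1.94 (ICC 0.05), with 1.71 at the BP value of 0.03. The comparison is feasible but can pick up only sizeable increases, so a null result must not be read as proof of safety. This should be changed; it does not affect the primary outcome.

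**What to change.** - State as the main harm analysis a comparison of recorded falls, and of likely fragility fractures, between the three randomised arms. Analyse by intention to treat, allowing for clustering by practice (practice-level summaries or a practice random effect), overall and in people over 75. Report risk or rate ratios with confidence intervals.
- Label the associations of falls with BP drugs, BP reduction and systolic BP level as exploratory.
- Under Stopping rules, add a table of falls by masked arm at each data extraction, built from the unlabelled arm groups already in the analysis table. This needs no unblinding. The field team should not produce it, since it delivers the interventions and knows the allocation. A masked table shows that arms differ but not which arm is which; that can still inform the review the protocol already provides for.
- State the limits: possible differences between arms in coding of falls (the reason for showing fractures alongside), and power for sizeable increases only.

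The cost is a few sentences and one extra table per extraction. No new data are needed.

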### Multivariate techniques

1. Using analysis of variance (ANOVA) models, compare the mean systolic BP of people with CKD stage three to five in the three arms of the study, before and after the interventions – the primary outcome measure of this study

2. Using ANOVA models, compare the confidence level of primary care practitioners in the management of people with CKD Stage three to five in the three arms of the study, before and after the interventions

3. Using multiple regression analyses, explore and quantify relations between independent variables (*e.g*., known demographics and risk factors, such as smoking status, level of cholesterol, obesity, anaemia and alcohol consumption) and dependent variables (*e.g*., CKD stage three to five, and diabetes).

### Longitudinal data analyses

The temporal dimension of the recorded clinical data collected contemporarily offers an opportunity for analyses of the natural history and the disease course of CKD. The data have an advantage of being free from bias from retrospective recall, and allow the follow-up of the full spectrum of the impact of contributory risk factors on and outcomes for people with CKD. A particular interest is the association between management of CKD, the rate of change of eGFR, falls, and the outcomes of CKD.

## Discussion

This study fills a gap in the literature about how to improve the management of CKD in primary care. This gap is worth filling, because interventions that can be administered in primary care should be able to slow the progression of CKD, and consequently reduce cardiovascular co-morbidity and the need for dialysis and transplantation.

The study is a pragmatic approach to quality improvement (QI) in CKD, and is intended to inform practitioners and the commissioners of care about the cost effectiveness of GaP and ABE in this disease area.

The ethical oversight of quality improvement projects remains a subject of much debate [48]. The study does not mandate any new intervention to be given to patients in participating practices, but rather promotes the implementation of best practice. Personalised decisions to treat patients will be made by individual practitioners in partnership with their patients, as now. Indeed, the primary research participants of the study are the participating practitioners rather than they patients they treat. This distinction has been recognised by the ethics committee that approved the study; our view is that studies of this potential size and impact should be part of the ethical approval process. Strictly, it is only the inclusion of randomisation which meant that this study required UK research ethics approval.

There are some weaknesses in the selection of BP as the primary endpoint; however these effects should be the same in each arm of the study. GPs will commonly check BP a second time if it is raised, but not if it is normal. There can consequently be a tendency for regression towards the mean in people with raised BP that is greater than in those with normal BP. This effect will need to be taken into account in the interpretation of the results. It is possible that people with raised BP will be under-detected.

A further problem with BP is that it tends to be recorded in primary care with marked end digit preference (EDP); *i.e*., a preference for recording a zero or five as the terminal digit [49]. EDP can make BP measurement a very blunt instrument, and make it harder to detect change. Although there has been improvement (*i.e*., a reduction) in EDP, especially in people with raised BP or cardiovascular co-morbidities, this remains a significant problem. Although, likely to influence each arm equally, EDP reduces the fidelity of our observations.

## Conclusion

This study should provide useful information about the influence of straightforward quality improvement interventions on the management of CKD; and if they are additive on the influences of financially incentivised QOF and the new national guidelines (NICE). The study will face all the challenges associated with working with routinely collected data, as well as the many confounding factors. We anticipate reporting whether the QI interventions tested have a place in improving the management of CKD.

## Appendix 1

Themes to be explored in the first year of the study

1. **Prevalence**. Prevalence of CKD, and prevalence by age band, for each of stage three to five CKD.

1.1 Practice prevalence (from serum creatinine records) compared with:

1.2 Population prevalence (from literature)

1.3 QOF prevalence (based on business case rules)

1.4 Standardised prevalence; deprivation and ethnicity recording

2. **Proteinuria recording**. Proportion of CKD patients with proteinuria estimation separately in diabetics and non-diabetics. Proportion of patients in whom proteinuria has been measured with albumin: creatinine ratio (ACR)>30 and >70 mg/mmol in non diabetics.

3. **BP**. Indicators of BP control.

3.1 Number of measurement in last 12 months

3.2 Most recent systolic and diastolic BP

3.3 Mean systolic and diastolic in last 6 months

3.4 Proportion meeting QOF standard, and NICE targets

4. **Angiotensin blockade in CKD**. Use of angiotensin modulating drugs (ACEI and ARB)

4.1 Total number of prescriptions

4.2 Use in CKD with proteinuria

4.3 Exemption coding

5. **Cardiovascular co-morbidities**. Prevalence, use of 10 year risk scoring.

6. **Process of delivering care**. Hints, tips, case-studies of how to achieve change (*e.g*., All hypertensives and those with CVS co-morbidity have a proteinuria test when having their blood tests.). Which primary care professionals are involved? Shift to primary care management.

7. **Motivation to change care**. Is CKD an illness? Are we inappropriately labelling much of the elderly population? Do the biomedical interventions do more good than harm?

8. **Improving the intervention**. How could the intervention be improved?

## Appendix 2

Themes for exploration in year two

1. **Programme fidelity and intervention exposure**. Has the implementation been feasible (programme fidelity) and what proportion of the practice have been interested in the feedback and results (intervention exposure)?

2. **How can the QI interventions be improved? **Suggested improvements to the interventions.

3. **Diabetes and CKD**. Prevalence of Diabetes and CKD and quality of management (comparing quality of management with QOF and national guidance, including new NICE guidance).

3.1 BP recording and control and use of angiotensin modulating drugs

3.2 HbA1c recording and value (compared with non-CKD diabetics, controlling for age and gender)

3.3 ACR (Albumin Creatinine ratio) in people with diabetes with CKD

3.4 Lipid management and use of statins and other medications for 1° and 2° prevention

3.5 Use of aspirin as primary and secondary prevention

4. **Cardiovascular co-morbidity**. We will look at risk factor management in people with cardiovascular disease, to include: use of lipid lowering therapy; use of aspirin; smoking cessation.

5. **Progression of CKD**. We will identify people with rapid progression.

6. **Anaemia and CKD**. We will flag people with anaemia who cross current NICE thresholds

7. **Avoiding harm**. We will look specifically for any evidence of increased numbers of falls; but are open to other unanticipated harmful consequences of the intervention.

8. **Good ideas**. The workshops will also seek to capture any examples of good practice and disseminate them across the group.

9. **Process of delivering care**. Any issues of call/recall of patients and concordance with therapy – especially angiotensin modulating drugs will be explored.

10. **Unexpected consequences**. We will try to identify any unexpected consequences of the interventions; good or bad.

## Appendix 3

Overview of the dataset extracted

Practice data

List size

QOF performance

Number and range of practice members engaged in CKD management

Pseudonymised practice indicator

Demographic

Age, gender

Ethnicity

Postcode (only first part is retained)

Index of deprivation (calculated in each practice from the postcode which is then deleted)

Cause of death & death

Clinical and laboratory

Serial measures of BP

Serial measures of serum creatinine concentration and eGFR

Co-morbid conditions (diabetes and its complications, ischaemic heart disease, heart failure, urinary obstruction)

Cardiovascular risk factors: smoking status; serum cholesterol and total cholesterol: HDL ratio; BMI, alcohol consumption; glycated haemoglobin and microalbuminuria in people with diabetes mellitus; urinalysis and total protein creatinine ratio; haemoglobin concentration

Lower urinary tract symptoms, prostate disease and urological factors which may reduce eGFR

Falls dataset (falls, likely fragility fractures, new diagnosis of osteoporosis)

Medications for optimal management that also impair renal function

Referral (to renal, diabetes, care of the elderly, urological and other specialties)

Other

Number of consultations in primary care
